The utility of patient health portals as a health promotion delivery system will be limited if uptake is low among patients in FQHC who may have issues with general literacy, health literacy, and technology-based literacy levels. In this aim, we will evaluate a tailored multi-modal educational campaign to increase the enrollment of MSHC patients in the UI Health Patient Portal. Currently, only 1% of MSHC patients are enrolled in the patient portal. The goal is to increase enrollment to 40% across the 3 years of the developmental trial to demonstrate the feasibility of delivering Mi QUIT CARE *via* the patient portal. The educational campaign will occur in three MSHC locations (Main, South Shore, and Englewood). The remaining three locations (Back-of-the-Yards, Cicero, and Humboldt Park) will serve as waitlist controls. The following strategies will be used to increase enrollment: (1) branding of the outreach initiative, “*My UI Health”*; (2) conducting a clinic campaign using materials tailored to low health literacy populations; (3) offering written provider recommendation and enrollment information during all clinical encounters; (4) mailing informational letters to all MSHC patients that includes enrollment instructions; and (5) offering onsite enrollment assistance provided by patient navigators. Trained patient navigators will assist clinic patients in enrolling in the patient portal *via* kiosks and secure iPads. After the data collection phase, the patient enrollment campaign will be conducted at the three waitlist control clinics.

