Study investigators will first evaluate patient portal enrollment considering all patients aged 18 and older who have had an office visit during the previous 24-month period to establish a baseline comparator. During the campaign, enrollment rates will be examined for each clinic to monitor increases in enrollment in the patient portal during the campaign period. We will compare enrollment rates for the intervention clinics vs. the control clinics. Further, we will evaluate whether additional targeted outreach efforts are needed for some patient groups by analyzing whether demographic factors (age, education, gender, race/ethnicity, last provider visit) are associated with portal enrollment. In addition, we will collect reasons for refusal among patients approached in the clinics by patient navigators. Data on enrollment will establish the feasibility of population-based engagement of health promotion interventions via the patient portal. Informed consent will not be required as this aim is part of a quality improvement project at the clinic to increase access to the patient portal. All analysis of portal uptake will be based on de-identified data.

*Aim 4: Test the acceptability, feasibility, and capacity of MSHC FQHC to deliver Mi QUIT CARE*.

We propose a Hybrid Type I effectiveness-implementation design grounded in RE-AIM (32). Hybrid I types are appropriate for evaluating outcomes associated with clinical intervention and implementation strategies (45). Led by our informatics team, our web application development will be spread across three phases: design, production, and testing/deployment. During the design phase of the study, our technical teams will work closely to refine and document all system specifications and requirements. System logic/rules will be generated. Wireframes, storyboards, interface mock-ups, schematics, and database designs will be produced. In the production phase, the technical team will build the application's site and database. The process will conclude with the testing and deployment phase in which the study and technical teams pass through multiple cycles of quality assurance. After the system is deployed to the live environment, the study and technical teams will stay engaged over the project's lifespan.

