All English-speaking adult patients at three MSHC locations (Main, South Shore, and Englewood) who smoke and are enrolled in the UI Health Patient Portal will be eligible for this pilot test. An equal number of patients (total *N* = 100) will be randomly selected from each location for the feasibility trial using a software program developed by programmers at the University of Illinois at Chicago. Human subject approval will be obtained before data collection, and formal informed consent obtained from participants.

Figure 3 displays an overview of the activities to be conducted in Aim 4 of the study. The intervention will be based on the 3 A's framework (Ask-Advise-Refer, [AAR]) (9, 11, 12). In the first phase of this aim, we will *Ask and Identity, All Smokers*. Project staff will review the electronic health record of the six participating clinic locations to identify all current smokers. Any patient without documented smoking status will be flagged for input during the subsequent clinical encounter. Next, we will *Advise a Quit Attempt*. A random selection of all smokers enrolled in the patient portal will be sent a signed letter from their provider via the portal. The letter will describe health risks associated with smoking, explain the availability of free treatments, strongly encourage the patient to make a quit attempt, and inform them that they will be receiving a call from the Illinois Tobacco Quitline. Patients will be informed that the ITQL will provide free smoking cessation counseling and nicotine replacement therapy (nicotine patches). An automated text or email message with a hyperlink to the portal login page will be generated and sent to patients to alert them of the message from their providers.

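### The 40% portal-enrollment goal is meant to show that Mi QUIT CARE can be delivered, but it is counted over all adults and no stated analysis gives the rate among smokers

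*Protocol article*

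**What the plan says.** All of this is in the Protocol article, Study Procedures.

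- **Aim 3, campaign.** The plan will evaluate "a tailored multi-modal educational campaign to increase the enrollment of MSHC patients in the UI Health Patient Portal". The starting point is given as "Currently, only 1% of MSHC patients are enrolled in the patient portal". The target and its purpose follow: "The goal is to increase enrollment to 40% across the 3 years of the developmental trial to demonstrate the feasibility of delivering Mi QUIT CARE" through the portal.
- **Aim 3, evaluation.** Enrollment is first measured "considering all patients aged 18 and older who have had an office visit during the previous 24-month period to establish a baseline comparator". It is then followed by clinic and compared between intervention and control clinics. To see which patient groups need more outreach, the plan will examine whether "demographic factors (age, education, gender, race/ethnicity, last provider visit) are associated with portal enrollment". The closing inference is broader: enrollment data are to establish that health promotion in general can be offered to a population through the portal.
- **Aim 4.** English-speaking adults at three clinics "who smoke and are enrolled in the UI Health Patient Portal will be eligible for this pilot test". On delivery, the plan says: "A random selection of all smokers enrolled in the patient portal will be sent a signed letter from their provider via the portal".
- **Aim 1.** Smoking status (current, former, never) is taken from the same electronic health record.

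**The concern.** The target is attached to one claim and counted in another population. The claim is that Mi QUIT CARE, a smoking-cessation intervention, can be delivered through the portal. The count covers adult patients whatever their smoking status. Never and former smokers who enroll move the figure toward 40% but cannot receive the intervention.

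Nothing else stated in the article fills the gap. Smoking status is missing from the factors to be related to enrollment. Aim 4 samples only smokers who are already enrolled, so its outcomes start after enrollment and cannot show how many smokers the portal misses.

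What is at stake is the use of the figure. The study prepares a fully powered trial, and the share of smokers on the portal caps the share that trial can contact by this route. An overall 40% would leave that share unknown.

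**Working it through.** **No figure to reproduce.** The article gives no derivation of 40% and attaches no sample size or test to it. The check is therefore how far the overall rate fixes the rate among smokers.

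**Inputs**

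- Overall enrollment T = 0.40 (Aim 3).
- Share of smokers s = 0.258, the multi-state tobacco-use figure for health centers of this type (Introduction). It stands in for Mile Square Health Center's own prevalence, which the article does not give.
- Range for s: 0.22 to 0.35, for the Chicago areas with the highest poverty and segregation (Introduction).
- Ratio r of smoker to non-smoker enrollment: not in the documents. The values below are assumptions.

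**Share of the count outside the target population.** 1 − 0.258 = 0.742, so about 74% of those counted could not receive the intervention.

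**Formula.** Let p be non-smoker enrollment and r·p smoker enrollment. Then T = s·r·p + (1 − s)·p, so p = T / [(1 − s) + s·r].

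**Results at s = 0.258, T = 0.40**

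| r (assumed) | (1 − s) + s·r | p, non-smokers | r·p, smokers | smokers, s from 0.22 to 0.35 |
|---|---|---|---|---|
| 1.1 | 1.0258 | 39.0% | 42.9% | 43.1% to 42.5% |
| 1.0 | 1.0000 | 40.0% | 40.0% | 40.0% |
| 0.9 | 0.9742 | 41.1% | 37.0% | 36.8% to 37.3% |
| 0.75 | 0.9355 | 42.8% | 32.1% | 31.7% to 32.9% |
| 0.5 | 0.8710 | 45.9% | 23.0% | 22.5% to 24.2% |

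**Cross-check by the weighted average.** Smoker rate = [T − (1 − s)·p] / s. With non-smokers at 45%: (0.40 − 0.742 × 0.45) / 0.258 = 0.0661 / 0.258 = 25.6%. With non-smokers at 50%: (0.40 − 0.371) / 0.258 = 11.2%.

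**Reading.** Prevalence matters little: across 22% to 35% the smoker rate at a given r moves by less than 2 points. The ratio matters most, and no analysis listed in the article would estimate it.

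**The case against.** The strongest defense is that the denominator fits the aim. Aim 3 is about portal uptake among patients receiving care, the campaign is offered to all of them, and the evaluation closes with a claim about health promotion in general. For that claim all adults is the right base. This stands, and it is why the all-adult goal should be kept. It does not cover the sentence that ties 40% to Mi QUIT CARE specifically.

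Second, the adult, 24-month denominator is stated for the baseline. Applying it to the 40% goal is an inference. It is the natural one, since a rise from 1% to 40% needs a common base and no other is given.

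Third, Aim 4 will identify all current smokers in the record at the six clinics and draw from those enrolled, so the parts of the missing rate will be at hand. That is true, but no statement commits to computing it.

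Fourth, the factor list is headed as demographic, and further covariates are ordinary detail for a full protocol or analysis plan. That is fair, and the absence of smoking status alone would be no finding. The point rests on a goal, a counted population and a purpose that the article itself states and that do not match.

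Two stronger readings are tempting and should be resisted:

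- **That smokers enroll less.** A reader might infer this because the Introduction links smoking to poverty and poor access to care, and portal use to the digital divide. The documents do not support it for this population. The Setting section puts 98% of patients at or below the poverty level, and the denominator contains only patients with a recent visit, so neither factor separates smokers from non-smokers as it might in the community. Smokers could also enroll more.
- **That 40% is a pass mark the study could wrongly pass.** The article calls it a goal, with no test or go/no-go rule. A probability of meeting it would rest on an invented true rate and clinic size, so none is given here.

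**Conclusion.** The concern holds in a limited form. The all-adult rate is a sound measure of general portal uptake. It is not evidence of the share of smokers the portal can reach, which is what a feasibility statement about Mi QUIT CARE needs.

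The size is unknown. If enrollment is unrelated to smoking, there is no discrepancy. At the assumed ratios of 0.9, 0.75 and 0.5, an overall 40% goes with 37%, 32% and 23% among smokers, all still far above the 1% baseline for patients overall. These figures rest on assumed ratios and a proxy prevalence. It does not follow that the future trial will be planned on a wrong share, because the investigators will hold the smoker lists and may use them. What can be said is that the plan as written does not commit them to. This is a worthwhile correction, not a fatal flaw.

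**What to change.** - Keep 40% over all adults with a visit in the previous 24 months as the goal for general portal uptake.
- In Aim 3, also report enrollment among adults charted as current smokers, by clinic and by arm (intervention or waitlist), at baseline and during the campaign. Show patients with undocumented smoking status separately. Give the same rate for English speakers, to match Aim 4 eligibility.
- Add smoking status to the factors related to enrollment.
- Base the Mi QUIT CARE feasibility statement, and the planning of the future trial, on the smoker rate.

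The cost is some wording and one more field in the de-identified Aim 3 extract, since Aim 1 already takes smoking status from the same record. The downsides are reliance on charted smoking status, a possibly less favorable figure, and less precision. At 25.8% smokers and the same rate, an interval would be about 1/√0.258 ≈ 2.0 times as wide as the all-adult one.

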### Setting

This multi-level intervention will be delivered via the University of Illinois Hospital and Health Sciences System (UI Health) Patient Portal, a cost-effective and sustainable intervention delivery system. Mi QUIT CARE will be conducted in six Mile Square Health Center (MSHC) clinics, a network of 13 community-located FQHCs, including school-based health centers. MSHC is co-owned and operated by UI Health. MSHC serves communities experiencing a high burden of pulmonary health morbidity and mortality associated with tobacco use. The majority of MSHC patients are Black (74%), live at or below the federal poverty level (98%), and are insured through Medicaid (55%, 10% are uninsured). MSHC has the infrastructure to complete the study and monitor the impact of the intervention on their patients' smoking and pulmonary health status over time. Metrics demonstrating implementation readiness include: (1) consistent assessment and documentation of smoking status in the electronic health record by providers; (2) current availability of a system-wide patient portal that can be used to communicate with patients regarding their care; (3) an established collaboration with the Illinois Tobacco Quitline as part of an existing smoking cessation program at MSHC, and (4) an existing patient navigation program for smoking cessation and lung cancer screening.

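### Aim 3 confines the portal-enrollment campaign to three clinics, yet one of its five strategies is a letter to all MSHC patients, which as worded includes the waitlist-control clinics

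*Protocol article*

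**What the plan says.** All of the following comes from Study Procedures, Aim 3, except where noted.

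- **Where the campaign runs:** "The educational campaign will occur in three MSHC locations (Main, South Shore, and Englewood".
- **Who the controls are:** "The remaining three locations (Back-of-the-Yards, Cicero, and Humboldt Park) will serve as waitlist controls".
- **When controls get the campaign:** "After the data collection phase, the patient enrollment campaign will be conducted at the three waitlist control clinics".
- **What the campaign consists of:** five items introduced by "The following strategies will be used to increase enrollment". They are branding, a clinic campaign with low-literacy materials, written provider recommendations at encounters, mailed letters, and on-site help from navigators.
- **Who receives the letters (item four):** "mailing informational letters to all MSHC patients that includes enrollment instructions".
- **What is compared:** "We will compare enrollment rates for the intervention clinics vs. the control clinics".

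The Setting section gives the scope of the name: "Mi QUIT CARE will be conducted in six Mile Square Health Center (MSHC) clinics, a network of 13 community-located FQHCs".

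**The concern.** A waitlist control is useful only if it goes without the intervention while outcomes are being collected. Here the one statement of who is mailed covers the control clinics. The letter carries instructions for achieving the outcome itself, portal enrollment, so it is an active component and not background information.

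The intervention-versus-control comparison is the only controlled contrast in Aim 3. If both groups are mailed, it no longer measures the campaign as a package, which is what Aim 3 sets out to evaluate. Analysis could not restore an unmailed comparison group afterwards, because a before-after change in the control clinics would mix the letter's effect with any time trend.

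**Working it through.** The article states no sample size, power or effect size for Aim 3, so there is no figure to reproduce. The check is textual, followed by one line of algebra.

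**1. Does the phrase cover the control clinics?** There are three possible scopes for the mailing.

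| Scope of the phrase | Support in the article | Control clinics mailed? |
|---|---|---|
| Whole network of 13 | Setting section; Aim 3's own baseline, "Currently, only 1% of MSHC patients are enrolled in the patient portal", where the term carries no clinic limit | Yes |
| The six study clinics | Aim 1 uses the MSHC name for the six participating sites | Yes |
| The three intervention clinics | Only by carrying over the earlier sentence on where the campaign takes place | No |

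The first two scopes both include Back-of-the-Yards, Cicero and Humboldt Park. Only the third keeps the controls unmailed, and the article does not state it for the letters. Where the article does mean just the three intervention clinics, as in the eligibility paragraph of Aim 4, it names them.

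**2. Do the neighbouring sentences agree with a mailing to all?** No. One sentence places the campaign in three clinics and another defers it in the other three. A letter to all MSHC patients is part of that campaign and is neither confined nor deferred. The statements cannot all be carried out as written.

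**3. What would the comparison estimate under the literal reading?** Let T be the effect of the full campaign on the enrollment rate in the intervention clinics and L the effect of the letter alone in the control clinics. Assume both groups share the same baseline b and the same background change d.

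- Intervention clinics: b + d + T
- Control clinics, not mailed: b + d, so the contrast is T
- Control clinics, mailed: b + d + L, so the contrast is T − L

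The shortfall equals L. For any L above zero the contrast is pulled toward no difference.

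**4. Illustration only.** The article gives a 1% starting level and a 40% goal. Suppose the intervention clinics reach the goal, the controls start at 1%, and nothing else changes. The contrast without a letter in the controls is 40 − 1 = 39 points. With an assumed letter gain of 2, 5 or 10 points it is 39 − 2 = 37, 39 − 5 = 34, or 39 − 10 = 29 points. These gains are assumptions with no basis in the article, and 40% is a three-year target, not an expected effect. The lines show the direction and the one-for-one relation, not a predicted size.

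**The case against.** The strongest reply is that the five strategies are the contents of the campaign, so the sentences before and after the list confine and defer every item, the letter included. On that view the phrase is loose wording for all patients of the three clinics. The provider-recommendation strategy also lacks a clinic limit, and nobody would take it to run in the control clinics.

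Part of this stands. The narrower reading is available, so a reader who infers that the controls will definitely be exposed goes further than the article does. But the analogy with provider recommendations is weak. Those happen at a clinic visit, so the site restriction reaches them naturally. A mailing is tied to no site, and this item carries its own explicit statement of recipients. Whoever prepares the mailing list would follow that statement.

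A second reply is that little depends on the contrast. The primary outcomes in the Data Analysis section are Reach and Impact, the Aim 4 patients come only from the three intervention clinics, and the 40% goal is judged against a pre-campaign baseline. Aim 3 is also described as quality improvement. This is correct and limits the consequence to the Aim 3 comparison. It does not remove the problem there.

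Two stronger inferences should be resisted:

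- **A percentage understatement.** It would need a letter effect that the article does not give, and it would treat the enrollment target as a true effect.
- **That mailing everyone is what stops the letter from being credited with an effect.** Restricting the mailing would not isolate the letter either, because it would remain bundled with four other strategies.

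**Conclusion.** The point holds as an internal contradiction in Aim 3 with a definite consequence if the mailing rule is followed as written. Controls would receive one of five components during the comparison period, and the contrast would estimate the other components added to the letter. It would fall short of the full campaign effect by the letter's effect in the control clinics.

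The size cannot be stated from the article. The direction, toward no difference, requires only that the letter has some positive effect there. The algebra assumes that baseline and background change are the same in both groups.

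Exposure of the controls is implied by the wording and is not documented conduct. The passage still needs correcting before any letter goes out, because an unmailed control group cannot be recovered afterwards.

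**What to change.** Reword the fourth strategy so that, until Aim 3 data collection ends, letters go only to patients of Main, South Shore and Englewood. State that patients of the three control clinics are mailed when the campaign is rolled out to those clinics, as already planned. Other MSHC patients can be mailed at the same time.

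The cost is a clinic filter on the mailing list and a later letter for those patients. The Ethics Statement indicates that Aims 3 and 4 had not begun, so the change could be made before any mailing.

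If a network-wide mailing is intended, keep it but say so openly. Describe the control condition as letter only, and state that the comparison estimates the effect of the remaining strategies over and above the letter. That costs one or two sentences, and it gives up the controlled estimate of the whole campaign.

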### Tobacco Cessation Treatments

In 2000, the U.S. Public Health Service clinical practice guideline, Treating Tobacco Use and Dependence, recommended that providers consistently identify and document patients' tobacco use status and treat tobacco users via the “5As” framework (Ask-Advise-Assess-Assist-Arrange) (6). Although effective, the 5As model is time-consuming and can be challenging to implement in high-volume clinical settings (7). A simplified version of the framework (Ask-Advise-Refer, [AAR]) was subsequently developed (8). When implemented in clinical settings, AAR has demonstrated effectiveness for increasing patient engagement with recommended treatment approaches such as state tobacco quitlines (9–12). State-run tobacco quitlines offer free telephone counseling and nicotine replacement for low-income smokers. The average quit rates among quitline users are 12.7%, increasing to 28.1% when counseling is combined with nicotine replacement (6). Despite the efficacy of provider interventions such as AAR for linking smokers to treatment, these interventions are underutilized in clinical settings.

FQHCs are required to report annually on their implementation and dissemination of evidence-based tobacco cessation per their Uniform Data Set (UDS) guidelines for FQHCs (5). The Centers for Disease Control and Prevention reports that, although 62.7% of outpatient visits included tobacco screening, only 20.9% of current tobacco users received counseling and 7.6% received a prescription for pharmacotherapy during their visit (13). Barriers to provider adherence to AAR practice guidelines are well-documented (i.e., time restraints) (7). As such, innovation in implementing AAR clinical practice guidelines is needed to facilitate the delivery of evidence-based smoking cessation treatments, especially in clinical populations disproportionately burdened by tobacco use.

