#### Refer

The provider letter will describe the benefits of smoking cessation, advise the patient to quit smoking, and notify them they will receive a call from the ITQL within the next 48 h. Once the patient views the electronic provider letter via the patient portal, an automated referral will be sent to the ITQL with the patient's name, phone number, and unique ID number. Patients will also be allowed to opt-out of the treatment engagement call.

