#### Treatment

A trained tobacco quitline counselor will call patients. Once reached, quitline counselors will assess the patient's readiness to quit smoking and provide an appropriate treatment plan. If interested in making a quit attempt, quitline counselors will provide smokers with an overview of the program, obtain cessation goals, recommend a treatment approach (counseling only or counseling + nicotine replacement therapy), and schedule the next session. The ITQL counseling program is based on the Freedom from Smoking (46, 47) program. It offers up to 6 weeks of free nicotine replacement (patches) to those 18 and older, medically eligible, and uninsured or on Medicaid. The American Lung Association operates the Illinois Tobacco Quit Line. Certified counselors speak both English and Spanish and have expertise in the treatment of diverse smokers.

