### Data Analysis

Consistent with RE-AIM (32), our primary outcomes will include Reach and Impact (Reach x Efficacy). We will obtain feasibility data from the patient portal. First, we will assess which patients received (opened) an electronically generated message from their providers advising them to make a quit attempt, describing free stop smoking services from the ITQL, and informing them about an upcoming call from the ITQL. All patients will be allowed to opt into the proactive ITQL counselor call. We will evaluate what percentage of patients opt-in to treatment and the demographic factors associated with the decision to accept linkage to the ITQL. Next, we will assess the percentage of patients who opted-in to treatment and were subsequently reached by the ITQL. Finally, we will evaluate the percentage of patients who engaged in stop smoking treatment (participated in more than 1 counseling call) and their quit outcomes. Patient receipt of treatment and self-reported quit rates will be obtained from the ITQL. The ITQL will provide a monthly report on patient engagement and quit rates. Statistical analyses (multivariable logistic regression models) will be conducted to determine demographic factors (age, race, gender, clinic) associated with receipt of the provider message and advice to quit smoking, receipt of treatment by the ITQL, and quit rates. One of our smoking cessation patient navigators will contact patients who opted-in to linkage to the ITQL and who were not reached by an ITQL counselor. Patient navigators will record barriers to quitline engagement that will be qualitatively analyzed. Data from this aim will refine implementation strategies and procedures in preparation for a fully powered randomized controlled trial.

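### Aim 4 patients are to be told without condition that the quitline will provide nicotine patches, although the article limits free patches by insurance and medical eligibility

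*Protocol article*

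**What the plan says.** The statement to patients is in the protocol article, Study Procedures, Aim 4: "Patients will be informed that the ITQL will provide free smoking cessation counseling and nicotine replacement therapy (nicotine patches"). It belongs to the description of the provider letter sent through the portal.

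The quitline's own rule is in the Treatment section: "It offers up to 6 weeks of free nicotine replacement (patches) to those 18 and older, medically eligible, and uninsured or on Medicaid".

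On who enters the pilot, Study Procedures, Aim 4 states that English-speaking adults at three clinics "who smoke and are enrolled in the UI Health Patient Portal will be eligible for this pilot test". A total of 100 are then randomly selected. No insurance or medical criterion is listed.

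The Refer section gives the next step: "Once the patient views the electronic provider letter via the patient portal, an automated referral will be sent to the ITQL". Patients may decline the call. The Data Analysis section makes the response an outcome: "We will evaluate what percentage of patients opt-in to treatment".

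The Setting section describes the patients of the whole system: most "live at or below the federal poverty level (98%), and are insured through Medicaid (55%, 10% are uninsured").

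**The concern.** Two statements about the same quitline, treatment and patients do not agree. One tells every recipient that patches will be provided. The other restricts free patches to a subgroup that pilot eligibility does not enforce.

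Two things are at stake, both modest. First, some participants would decide about the quitline call on an offer broader than the one open to them, in a letter signed by their own provider. Second, the share who accept the call is one of the pilot's feasibility results and is meant to inform the later full trial. A figure obtained under a broader offer may not carry over exactly to a correctly worded letter.

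**Working it through.** The article gives no sample-size, power or error-rate figure on this point, so there is nothing to reproduce. The check compares texts, followed by a rough size.

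**Step 1. Patch conditions against Aim 4 eligibility.**

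| Condition for free patches (Treatment) | Guaranteed by Aim 4 eligibility (Study Procedures)? |
|---|---|
| Aged 18 or older | Yes, the pilot admits adults only |
| Medically eligible | No, no medical criterion |
| Uninsured or on Medicaid | No, no insurance criterion |

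One of three conditions is secured. The message is accurate for a participant only if the other two also hold.

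**Step 2. Order of events.** The letter is sent, the patient views it, the referral goes out, and the counselor calls. The letter is described in Study Procedures, in Refer and in Data Analysis, and none of these descriptions adds a patch condition. The first described point at which patch use is considered for the individual is the call itself, where the counselor will "recommend a treatment approach (counseling only or counseling + nicotine replacement therapy"). That comes after the patient has had the letter and the chance to decline. Informed consent is also planned, but its content is not shown.

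**Step 3. Size, system-wide.** Inputs from Setting: 55% Medicaid, 10% uninsured.

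- Meeting the insurance condition: 55 + 10 = 65%.
- Apparently outside it: 100 - 65 = 35%.

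The 35% is an upper figure for the insurance condition in that population, because people who hold Medicaid together with other coverage cannot be counted from the figures given. Medical ineligibility could add to the number who do not qualify. No rate is given for it, so none is used here.

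**Step 4. Would anyone in the pilot be affected?** The insurance mix of portal-enrolled smokers at the three clinics is not stated, so the share q outside the insurance condition is an assumption, shown over a range. With n = 100 treated as independent draws, the expected number is 100q and the chance of at least one is 1 - (1 - q)^100.

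| Assumed q | Expected number of 100 | Chance of at least one |
|---|---|---|
| 5% | 5 | 1 - 0.95^100 = 0.994 |
| 10% | 10 | 1 - 0.90^100 = 0.99997 |
| 20% | 20 | above 0.9999 |
| 35% (system-wide figure carried over) | 35 | above 0.9999 |

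Even if the pilot share were far below the system-wide figure, some participants would almost certainly fall outside the rule.

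**Step 5. What it touches.** The opt-in percentage is recorded after the message, so it is the step most directly exposed. Free counseling is not contradicted for anyone.

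**The case against.** The strongest reply is that the letter is not shown. The article reports its content in one sentence, and a condensed article may leave an eligibility clause to the letter or the consent form. The full terms appear a few paragraphs later, so the limit is disclosed to readers. The materials are still to be developed and tested, and the counselor settles the treatment plan at first contact.

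Much of this stands. It would be too strong to infer that patients will in fact be misinformed, because the final letter and consent may carry the condition. The counselor's recommendation also limits the harm. It does not reconcile the two statements, though: the article does not merely omit a condition, it states what patients will be told and elsewhere states a rule that makes this untrue for some of them. It could also be said that the word free attaches only to counseling. The sentence would still say that the quitline will provide patches, and the only provision the article describes is the restricted one.

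Three stronger readings are tempting and not supported:

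- A reader might infer that about 35 of the 100 pilot patients will not qualify. The 35% describes the whole system, and portal-enrolled smokers at three clinics may differ.
- A reader might use the statement that "The average quit rates among quitline users are 12.7%, increasing to 28.1% when counseling is combined with nicotine replacement" to argue that the wording bears heavily on outcome. Those rates concern treatment received, not how an invitation is phrased, and nothing in the article shows how patch wording changes opt-in.
- A reader might combine the poverty and insurance percentages to claim that many poor patients are wrongly promised patches. Poverty is not a patch condition, so the calculation answers a different question.

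**Conclusion.** Wrong as written, minor. As described, the message is unconditional while the quitline's rule is conditional, and Aim 4 eligibility secures only age. Following the description literally would give some participants an inaccurate offer and could modestly affect the opt-in figure. No sample size, error rate or analysis is affected.

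System-wide, up to about 35% may fall outside the insurance condition, and the pilot share is unknown. The conclusion does not need that exact share. It needs only that some selected patients have other insurance or are medically ineligible, and that the letter and consent follow the article's description.

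**What to change.** Before IRB submission for Aim 4, word the provider letter and the consent text along these lines: free counseling, and free patches if you qualify under the quitline's rules (medically eligible, and either on Medicaid or without insurance). Amend the sentence in the Aim 4 description to match.

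Check that readers understand the conditional clause in the interviews already planned under Aim 2 for the tailored materials (25 smokers and 10 providers). Those materials include the provider communication and the description of the quitline. Leave the broad pilot eligibility as it is, since it suits a Reach outcome.

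The cost is one clause in a letter that need not yet be final: the Ethics Statement indicates that Aim 4 research has not begun and that IRB review must come first. The downside is that conditional wording may be slightly less persuasive. In return, the opt-in figure would reflect the offer actually available.
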